# Noisy Galvanic Vestibular Stimulation Combined With a Multisensory Balance Program in Older Adults With Moderate to High Fall Risk: Protocol for a Feasibility Study for a Randomized Controlled Trial

**DOI:** 10.2196/32085

**Published:** 2021-10-05

**Keywords:** older adult, balance, rehabilitation, noisy galvanic vestibular stimulation, nGVS, brain stimulation

## Abstract

**Background:**

Reduced mobility and falls are common among older adults. Balance retraining programs are effective in reducing falls and in improving balance and mobility. Noisy galvanic vestibular stimulation is a low-level electrical stimulation used to reduce the threshold for the firing of vestibular neurons via a mechanism of stochastic resonance.

**Objective:**

This study aims to determine the feasibility of using noisy galvanic vestibular stimulation to augment a balance training program for older adults at risk of falls. We hypothesize that noisy galvanic vestibular stimulation will enhance the effects of balance retraining in older adults at risk of falls

**Methods:**

In this 3-armed randomized controlled trial, community dwelling older adults at risk of falling will be randomly assigned to a noisy galvanic vestibular stimulation plus balance program (noisy galvanic vestibular stimulation group), sham plus balance program (sham group), or a no treatment group (control). Participants will attend the exercise group twice a week for 8 weeks with assessment of balance and gait pretreatment, posttreatment, and at 3 months postintervention. Primary outcome measures include postural sway, measured by center of pressure velocity, area and root mean square, and gait parameters such as speed, step width, step variability, and double support time. Spatial memory will also be measured using the triangle completion task and the 4 Mountains Test.

**Results:**

Recruitment began in November 2020. Data collection and analysis are expected to be completed by December 2022.

**Conclusions:**

This study will evaluate the feasibility of using noisy galvanic vestibular stimulation alongside balance retraining in older adults at risk of falls and will inform the design of a fully powered randomized controlled trial.

**Trial Registration:**

New Zealand Clinical Trials Registry (ACTRN12620001172998); https://www.anzctr.org.au/Trial/Registration/TrialReview.aspx?id=379944

**International Registered Report Identifier (IRRID):**

DERR1-10.2196/32085

## Introduction

### Background

The contribution of age-related decline in postural responses to reduced mobility and falls in older adults is well established [1-4]. The mechanisms underlying this deterioration are complex but are thought to include impaired function and processing of sensory information from the visual, vestibular, and somatosensory systems. The vestibular system is perhaps the least understood of these balance systems. However, rich connections between the hippocampus, cerebellum, and brainstem suggest that treatments designed to enhance the vestibular system have the potential to improve postural stability and balance [5-8].

Noisy galvanic vestibular stimulation is a subsensory galvanic stimulation delivered with a superimposed Gaussian noise signal. The proposed mechanism of action is based on the principle of “stochastic resonance,” in which noisy galvanic vestibular stimulation enhances weak sensory input signals from the vestibular apparatus [9,10]. This then enhances vestibular perception and vestibulospinal reflex function, both essential components of the sensory feedback loop for balance [11-13].

All sensory systems decline with age [14]; however, there is strong evidence that balance training can reduce the risk of falls in older adults and improve clinical tests of stability [15-17]. Although there are known benefits of rehabilitation programs for balance retraining, less is known about the effect of noisy galvanic vestibular stimulation on postural control [18,19]. Emergent research in humans suggests immediate benefits to static balance. Inukai et al [20] reported immediate improvements in standing balance when noisy galvanic vestibular stimulation was administered to healthy older adults, and Iwasaki et al [4] demonstrated a similar positive effect in patients with bilateral vestibular dysfunction. There is some evidence that this benefit may be sustained. Fujimoto et al [21] examined the effect of 30 minutes of noisy galvanic vestibular stimulation on balance and found that a positive effect was maintained for up to 3 hours after exposure to the intervention. These improvements were further enhanced by a subsequent 30-minute exposure, which also sustained the beneficial effects. However, this sustained effect has not been replicated consistently in other studies; Inukai et al [22] found a poststimulation effect in contrast to Nooristani et al [23] and Keywan et al [24] who did not. A secondary analysis by Fujimoto et al [21] discovered that noisy galvanic vestibular stimulation resulted in significantly greater improvements in participants who were more unsteady on initial assessment [25]. This suggests that either noisy galvanic vestibular stimulation has a greater effect on the hypofunctional vestibular system or that different noisy galvanic vestibular stimulation parameters and experimental designs play a role in these findings. Noisy galvanic vestibular stimulation has also shown positive effects on walking balance, with Wuehr et al [12] and Iwasaki et al [26] finding that noisy galvanic vestibular stimulation resulted in an immediate positive effect on gait and in adults with bilateral vestibular pathology. However, to date, there are no studies of noisy galvanic vestibular stimulation in older adults who present with a fall risk, and no studies have investigated the repeated application of noisy galvanic vestibular stimulation as a clinical intervention. No study has investigated the augmented effect of concurrent noisy galvanic vestibular stimulation and balance rehabilitation to improve stability. We plan to redress these limitations by examining the impact of a balance rehabilitation program augmented with noisy galvanic vestibular stimulation in older adults at risk of falls.

### Objectives

This study aims to assess the feasibility of a future definitive randomized trial examining the effect of balance rehabilitation augmented with noisy galvanic vestibular stimulation in older adults at risk of falls. The primary objective is to assess the feasibility of the study process, including (1) rate of participant recruitment, conversion, and retention; (2) feasibility of screening processes; (3) utility of data collection and outcome measures; and (4) acceptability and suitability of the intervention and study procedures.

Our secondary objectives are to (1) evaluate participant opinions of the intervention as a basis for refinement of the definitive trial; (2) select a responsive and meaningful outcome measure; and (3) to inform the power and sample size calculations for the future full randomized controlled trial.

## Methods

### Trial Design

This study is a 3-armed randomized controlled trial design with a qualitative component. A total of 72 participants will be randomly allocated in a 1:1:1 ratio to a noisy galvanic vestibular stimulation group, sham group, or no intervention control group. Recruitment will close once 24 participants have been recruited into the noisy galvanic vestibular stimulation arm. Outcome assessment will occur at baseline (week 1), posttreatment (week 10) and at the 3-month follow-up posttreatment (Table 1).

**Table 1 table1:** Standard Protocol Items-Recommendations for Interventional Trials tabulation of study enrollment, interventions, and assessments.

Study events		Study period						
		Enrollment	Postallocation					Closeout
			Week 1	Week 2-9	Week 10	Week 22		
**Eligibility screen**								
	STEADI^a^ questions	✓						
	Three-step command	✓						
	Demographics (age, sex, and ethnicity)	✓						
	Exclusion screen for nGVS^b^	✓						
	Informed consent	✓						
	Written informed consent		✓					
	Allocation	✓						
**Assessments**								
	Montreal Cognitive Assessment		✓					
	Activities-specific balance confidence		✓		✓	✓		
	Center of pressure		✓		✓	✓		
	Single and dual task gait		✓		✓	✓		
	Timed Up and Go		✓		✓	✓		
	Four-Stage Balance Test		✓		✓	✓		
	Functional Gait Assessment		✓		✓	✓		
	30-second chair stand test		✓		✓	✓		
	Triangle completion task		✓		✓	✓		
	4 Mountains Test		✓		✓	✓		
	Adverse event monitoring			✓				
	Intervention fidelity monitoring			✓				
	Semistructured interviews				✓			
**Intervention**								
	Exercise+nGVS			✓				
	Exercise+sham nGVS			✓				
	Exercise (control)						✓	

^a^STEADI: Stop elderly accidents, deaths, and injuries.

^b^nGVS: noisy galvanic vestibular stimulation.

Semistructured interviews posttreatment will investigate the acceptability of the research processes and the intervention from the perspectives of study participants and physiotherapists.

### Participant Recruitment and Eligibility Criteria

#### Recruitment

Older adults will be recruited from the community in a staged manner to determine the feasibility of recruitment methods. Suitable candidates will be approached via newspaper advertisements, local medical practices, newsletters targeting older adult community groups, retirement villages, social media, community notice boards, presentations to local groups, and professional networks. Data will be collected on the efficacy of each method in terms of response rate, proportion of respondents who were eligible, eligible respondents who subsequently consented to the study, and the number of participants who completed the study.

#### Screening

People interested in participating will contact a member of the research team via telephone or email. Initial screening and eligibility will be assessed by a trained research assistant via telephone and data entered into the REDCap database. Eligible participants who provide consent will be enrolled into the study. 

#### Inclusion Criteria

Participants are eligible for inclusion if they meet the following criteria: (1) aged ≥65 years or Maori or Pasifika aged ≥55 years, (2) independently living in the community, (3) considered at risk of falls based on the stop elderly accidents, deaths and injuries (STEADI) fall screening questions (Textbox 1) [27], and (4) able to stand independently for 5 minutes and ambulate for 10 m with or without a walking aid.

Stop elderly accidents, deaths and injuries (STEADI) fall risk screening questions.
**Screening questions (answering yes to any of these questions indicates a fall risk)**
Have you fallen in the past year?Do you feel unsteady when standing or walking?Do you worry about falling?

#### Exclusion Criteria

Participants will be excluded if any of the following criteria are present: (1) diagnosis of a neurological condition, (2) pacemaker, (3) metal implants in the head or neck, (4) vertigo, (5) current diagnosis of migraine, and (6) cognitive impairment to the extent that they are unable to follow a 3-step command on the telephone.

#### Randomization

Participant group allocation will be by stratified random computer generation using a “minimization” algorithm in MinimPy (Msaghaei) to stratify groups by age, sex, and fall history in the past 6 months [28-30]. Allocation will be concealed in an opaque envelope identified only by the identification number of the participant and given to the participant after the initial assessment. Participants will be requested to open the envelope only after exiting the testing room. A contact number will be included in the envelope if participants wish to discuss their allocation.

#### Blinding

The noisy galvanic vestibular stimulation and sham group participants, assessors, therapists, and data analysts will be blinded to the group allocation. Measures will be taken to minimize the potential for the assessor and treating therapist to become unblinded. This will include avoiding discussions about the participants in front of the assessor and treating therapist. When participants are contacted to make appointments for the assessment, the team members involved will use this opportunity to remind participants not to reveal details of any treatment they have received to the assessor. A register of the unblinding events will be maintained.

#### Assessment

Outcome measures will be collected by a single investigator who will be blinded to the allocation and not involved in any aspect of the intervention.

#### Data Collection Methods

Once participants are recruited to the study and have given consent, they will attend three assessments at baseline, posttreatment, and at the 3-month follow-up (Table 1). Assessors will be trained in a protocol by a member of the research team who is familiar with the testing procedures. Assessments will be audited for quality and data completeness and checked for precision by the project manager once 10% of the data has been collected. A summary of the checks will be provided to the data monitoring committee. Any reports of adverse events will be reported and discussed at the monthly steering committee meeting.

### Outcomes

#### Participant Characteristics

The participant population will be described using demographic data, anthropometric data, including weight and height, the Montreal Cognitive Assessment, a brief cognitive screening tool [31], and the Activities Balance Confidence Scale, a structured questionnaire measuring an individual’s confidence performing specific activities [31].

#### Postural Sway Parameters

Postural sway will be calculated from center of pressure (COP) excursions on a force plate [4] (AMTI) in eyes open and eyes closed conditions. COP values of velocity, area, and root mean square during static standing have been shown to be precise, quickly administered assessments [32,33], with minimal ceiling and floor effects [34,35], and excellent sensitivity in the identification of older adult fallers [36-38]. In addition, we will investigate the relationship between the COP excursion and velocity and acceleration profiles of the head.

#### Gait and Mobility Performance–Based Measures

Performance-based measures of balance, gait, and leg muscle strength will indicate change in function and postural control. These tests are widely used in research for older adults with and without pathology, and all have norm-referenced values and robust clinimetric properties.

Gait will be measured using a 7 m long × 0.6 m–wide instrumented walkway, GAITrite, gold software version 3.2b, (CIR systems), in both single and dual task conditions [39]. Spatiotemporal parameters of interest include step velocity, length, width, double support time, and variability [40,41]. In addition, we will investigate the relationship between these spatiotemporal measures and the velocity and acceleration profiles of the head. A 9-camera motion capture system sampled at 200 Hz will record 3D kinematic data during the balance and gait measures. The 3D kinematic data will be exported to MATLAB (MathWorks, Inc) where a 6 degrees of freedom model will be constructed from shoulder and head marker position data. The model will consist of two triangles in 3D space, the first one corresponding to the shoulders and the second one for the head. The time series for the roll, pitch, and yaw angles of the head will be calculated with respect to the shoulders. Linear displacement across the mediolateral and anterior-posterior axes and the angular displacement about the vertical axis will be computed from these time series for a quantitative analysis of the head movement.

A range of mobility performance measures will be used. The Functional Gait Assessment assesses balance during walking under different conditions (speed change, head turn, pivot turn, obstacle clearance, and narrow base) [42,43]. The 30-second chair stand test measures functional leg strength. Participants will be asked to stand up from a chair and sit back down as often as they can within 30 seconds [44]. The Timed Up and Go test is a simple test used to assess the mobility of a person and requires both static and dynamic balance. It involves timing a person rising from a chair, walking 3 m, turning around, walking back to the chair, and sitting down. The Timed Up and Go test is considered a valid, reliable, and sensitive measure of mobility and balance in older adults [45,46]. For the Four-Stage Balance Test, participants are asked to stand in 4 progressively more challenging positions for 10 seconds with their eyes open and without using an assistive device. If the patient can hold a position for 10 seconds without moving their feet or needing support, they go on to the next position. Otherwise, the test is stopped. An older adult who cannot hold the tandem stance for 10 seconds is considered at increased risk of falling [47].

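### Linear head displacement is to be derived from head-on-shoulder angles, which carry no position and leave out motion that head and trunk share

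*Protocol article*

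**What the plan says.** The processing of the motion-capture data is described only in the protocol article, under Gait and Mobility Performance–Based Measures. The recording itself is full: "A 9-camera motion capture system sampled at 200 Hz will record 3D kinematic data during the balance and gait measures". From it, "a 6 degrees of freedom model will be constructed from shoulder and head marker position data". The geometry is given as follows: "The model will consist of two triangles in 3D space, the first one corresponding to the shoulders and the second one for the head". Two sentences then fix the derived variables. The first is "The time series for the roll, pitch, and yaw angles of the head will be calculated with respect to the shoulders". The second is "Linear displacement across the mediolateral and anterior-posterior axes and the angular displacement about the vertical axis will be computed from these time series".

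Two analyses are to use head motion. Under Postural Sway Parameters, "we will investigate the relationship between the COP excursion and velocity and acceleration profiles of the head". Under Gait and Mobility Performance–Based Measures, "we will investigate the relationship between these spatiotemporal measures and the velocity and acceleration profiles of the head". Neither sentence says whether the head quantities are linear or angular, or in which reference frame they are expressed.

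**The concern.** The only series named before the displacement sentence are three angles of the head relative to the shoulders. An angle series says how the head is oriented on the trunk, not where the head is. The article gives no neck pivot and no lever length that could turn one into the other. If both were assumed, the result would still be movement relative to the shoulders, and any motion that head and trunk make together would cancel.

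That shared motion matters for the two planned associations. The article uses COP excursion as its measure of postural sway, which involves the body as a whole. If the head signal is shoulder-referenced, whole-body sway is on one side of the association and has been subtracted from the other. A weak association could then come from the reference frame and say little about how the participants control the head.

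**Working it through.** The plan states no figure on this point, so there is none to reproduce. The check has two parts: a reading of the stated derivation, and a geometric illustration of how much could be lost.

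**1. What the derivation can yield.** Write the head position in the laboratory as: shoulder position + (shoulder orientation applied to the head's position relative to the shoulders).

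- Roll, pitch and yaw relative to the shoulders contain none of these positions. Linear displacement therefore cannot be computed from them alone.
- Angular displacement about the vertical axis, relative to the shoulders, does follow from the yaw series. That part of the sentence is sound.
- If the relative translation from the six-degrees-of-freedom model were used in place of the angles, position would be available, but the shoulder terms would still be missing. When head and trunk move as one, relative displacement is zero.

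**2. Inputs for the illustration.** From the article: head and shoulder markers at 200 Hz, and the walkway length ("Gait will be measured using a 7 m long × 0.6 m–wide instrumented walkway"). Everything else is assumed: ankle to neck base L = 1.35 m; neck base to head marker l = 0.20 m; body sway amplitude 0.5 or 1.0 degree at 0.3 Hz; neck amplitude 0 to 10 degrees at 0.5 Hz; in gait, neck pitch ±5 to ±20 degrees, sideways trunk amplitude 2 to 5 cm and neck roll 1 to 5 degrees.

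**3. Formulas (one plane).** With body angle b and neck angle n:

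- head displacement in space = L·sin(b) + l·sin(b + n)
- displacement recoverable from the relative angle, given l = l·sin(n)
- share explained = 1 − var(head − recoverable) / var(head)

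**4. Standing, rigid neck (n = 0).** At 1 degree of sway the amplitude is 1.55 m × sin(1°) = 27.05 mm, and the root mean square is 27.05/√2 = 19.1 mm. At 0.5 degree the root mean square is 9.6 mm. The relative angle gives 0 mm in both cases.

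**5. Standing, with neck motion.** Worked case, 1 degree of sway and 3 degrees of neck motion: the recoverable root mean square is 200 mm × sin(3°)/√2 = 7.40 mm, and the head root mean square is 20.51 mm. The two motions have different frequencies and are uncorrelated, so the share explained is (7.40/20.51)² = 13%. Share explained over the range:

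| Neck amplitude | Sway 0.5° | Sway 1.0° |
|---|---|---|
| 0° | 0% | 0% |
| 1° | 6% | 2% |
| 3° | 37% | 13% |
| 5° | 62% | 29% |
| 10° | 87% | 62% |

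**6. Gait, anterior-posterior.** The recoverable peak-to-peak range is 2·l·sin(n). At ±5 degrees it is 0.035 m, and 0.035/7 = 0.5% of the walkway. At ±20 degrees it is 0.137 m, or about 2%.

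**7. Gait, mediolateral.** The recoverable amplitude is l·sin(n). It is 3.5 mm at 1 degree and 17.4 mm at 5 degrees. Against trunk amplitudes of 50 mm and 20 mm, this gives 3.5/50 = 7% at the low end and 17.4/20 = 87% at the high end.

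**The case against.** The best defence is that the displacement sentence is compressed. A six-degrees-of-freedom model has three translations as well as three rotations, so position is available within it, and a journal article need not set out a processing script. This stands in part: the authors may well intend to use the model's translations. But the sentence names the angle series as the source, and the only frame mentioned is the shoulders. Shoulder-referenced translation would still remove shared motion. The text therefore states something that cannot be done as written, which is more than an omitted detail.

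Head-on-trunk angles are also a legitimate measure in their own right. That stands, and the fix keeps them.

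Four stronger readings are tempting, and the document does not support them:

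- A reader might infer that the head velocity and acceleration in the two associations will come from the relative angles. The article ties only the displacements to those series. Relative angular velocity and acceleration could be obtained by differentiation, but the source and frame of the planned quantities are not stated. The problem is a risk, not a documented error in those analyses.
- A reader might infer that most or all head motion would be lost. That holds for a nearly rigid neck or for forward progression in gait, but not across the whole assumed range.
- A reader might infer that pitch and roll are discarded. All three angle series are calculated; only the angular displacement summary is confined to the vertical axis.
- A reader might infer that the choice of primary outcome for the definitive trial would be misled. Statistical Methods confines the responsiveness metrics to postural control outcomes. Head motion is not named there, in the abstract's primary measures, in Table 1, in the objectives or in the success criteria.

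**Conclusion.** The point holds for linear displacement: it cannot be obtained from head-on-shoulder roll, pitch and yaw without an assumed pivot and lever length, and what could then be obtained excludes motion common to head and trunk. This follows from the wording and needs no numerical assumption. Because the same section is the only account of how head movement is derived, the COP-to-head and gait-to-head associations are exposed to the same reference-frame problem, although the text does not commit them to it.

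The size is illustrative only. It rests on an assumed two-segment geometry and assumed sway and neck amplitudes, and runs from complete loss with a rigid neck to a minor loss when neck motion is large relative to sway. The consequence is confined to an additional exploratory analysis. The raw data are adequate; the fault lies in the described derivation.

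**What to change.** In Gait and Mobility Performance–Based Measures, replace the displacement sentence with a statement that linear head displacement, velocity and acceleration are computed from the head-marker positions in the laboratory frame. Add that these are the quantities used in the COP and gait associations, with a matching cross-reference under Postural Sway Parameters. Keep the roll, pitch and yaw of the head relative to the shoulders, labelled as a separate measure of head-trunk coordination.

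The cost is a small change to the MATLAB processing and about two sentences of text. The head and shoulder markers are already to be recorded in both the balance and the gait tests, so no new data, equipment or visits are needed, and recordings already made can be reprocessed.
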